## Abstract

**Background:**

The majority of patients with suspected acute coronary syndrome presenting to the emergency department will be discharged once myocardial infarction has been ruled out, although a proportion will have unrecognised coronary artery disease. In this setting, high-sensitivity cardiac troponin identifies those at increased risk of future cardiac events. In patients with intermediate cardiac troponin concentrations in whom myocardial infarction has been ruled out, this trial aims to investigate whether outpatient computed tomography coronary angiography (CTCA) reduces subsequent myocardial infarction or cardiac death.

**Methods:**

TARGET-CTCA is a multicentre prospective randomised open label with blinded endpoint parallel group event driven trial. After myocardial infarction and clear alternative diagnoses have been ruled out, participants with intermediate cardiac troponin concentrations (5 ng/L to 99th centile upper reference limit) will be randomised 1:1 to outpatient CTCA plus standard of care or standard of care alone. The primary endpoint is myocardial infarction or cardiac death. Secondary endpoints include clinical, patient-centred, process and cost-effectiveness. Recruitment of 2270 patients will give 90% power with a two-sided *P* value of 0.05 to detect a 40% relative risk reduction in the primary endpoint. Follow-up will continue until 97 primary outcome events have been accrued in the standard care arm with an estimated median follow-up of 36 months.

**Discussion:**

This randomised controlled trial will determine whether high-sensitivity cardiac troponin-guided CTCA can improve outcomes and reduce subsequent major adverse cardiac events in patients presenting to the emergency department who do not have myocardial infarction.

**Trial registration:**

ClinicalTrials.gov Identifier: NCT03952351. Registered on May 16, 2019.

**Supplementary Information:**

The online version contains supplementary material available at 10.1186/s13063-023-07431-9.

## Background

Patients with acute chest pain account for a tenth of all presentations to the emergency department and up to 40% of unplanned hospital admissions, with their assessment placing a major burden on health care resources [1–3]. Current assessment strategies focus on ruling in or ruling out acute myocardial infarction through clinical assessment, electrocardiography and serial cardiac troponin testing. Once myocardial infarction is ruled out, most patients are discharged from hospital without further investigation or treatment, even though a substantial proportion may have underlying coronary artery disease. Prior research suggests that use of high-sensitivity assays to quantify cardiac troponin concentrations within the normal reference range [4–8] can improve the risk stratification of patients with acute chest pain and may help clinicians identify those who would benefit most from further investigation and treatment.

Patients with cardiac troponin concentrations below the 99th centile upper reference limit on serial testing do not have myocardial infarction but may still have underlying coronary artery disease [9]. Unless these patients have ongoing pain or dynamic electrocardiogram changes, they are likely to be discharged from the emergency department [10] without a consistent approach to follow-up or further investigation. Although patients in whom myocardial infarction is excluded are at low risk of major adverse cardiovascular events in the short term [10], high-sensitivity cardiac troponin concentrations can refine risk prediction and identify those who may benefit from preventative therapies or coronary revascularisation [11].

We previously reported that patients with cardiac troponin I concentrations < 5 ng/L are at very low risk, with a negative predictive value of 99.6% for a composite endpoint of myocardial infarction or cardiac death at 30 days [5]. We have subsequently verified the effectiveness of this risk stratification threshold in an individual patient-level meta-analysis of 22,457 patients from nine countries, demonstrating that cardiac troponin I concentrations were < 5 ng/L in 49% of patients, of whom less than 5 per 1000 patients had a myocardial infarction or cardiac death at 30 days [8]. Incorporation of this risk stratification threshold into an early rule out pathway for patients with possible myocardial infarction increases the proportion of patients discharged safely from the emergency department by 21% [10]. However, patients without myocardial infarction and intermediate high-sensitivity cardiac troponin concentrations between 5 ng/L and the 99th centile upper reference limit are 10 times more likely to have a major cardiac event at 1 year compared to those with a concentration < 5 ng/L (5.3% versus 0.7%; adjusted odds ratio, 0.23 [95% confidence interval, 0.19 to 0.28]) [5, 8].

Similar approaches are now used in multiple accelerated diagnostic pathways [12, 13], and the use of separate risk stratification and diagnostic thresholds is now recommended by both the European Society of Cardiology (ESC) [14] and National Institute for Health and Care Excellence (NICE) guidelines [15]. Up to a third of patients have intermediate cardiac troponin concentrations, and the ESC guideline recommends clinicians consider further observation and investigation in these patients [11]. However, it is not clear what further investigation should be undertaken, and there is currently no evidence that any particular investigation can alter clinical outcomes.

We postulate that patients with acute chest pain and intermediate-risk high-sensitivity cardiac troponin concentrations will benefit from further investigation for coronary artery disease soon after discharge.

## Methods and design

### Study design

TARGET-CTCA is a multicentre prospective randomised open-label blinded endpoint (PROBE) parallel group event driven multicentre trial assessing superiority of computed tomography coronary angiography (CTCA) on the risk of myocardial infarction or cardiac death in patients with intermediate cardiac troponin concentrations discharged from the emergency department after exclusion of myocardial infarction compared to standard care. We recruited from emergency departments in 14 hospitals across 9 sites in the UK (Supplementary Table 1). The SPIRIT reporting guidelines was used (Supplementary file) [16].

### Study objectives

The primary objective of the study is to determine whether the use of high-sensitivity cardiac troponin testing to risk stratify and target CTCA improves outcomes in patients presenting to hospital with suspected acute coronary syndrome in whom myocardial infarction is ruled out. The secondary objectives are to determine whether this approach is safe and cost-effective and improves patients’ quality of life or symptoms.

### Primary endpoint

The primary endpoint is a composite of myocardial infarction or cardiac death. Myocardial infarction is defined according to the Fourth Universal Definition of Myocardial Infarction [17] whilst cardiac death is defined as death resulting from an acute myocardial infarction, sudden cardiac death, or death due to heart failure [18]. Both myocardial infarction and cause of death will be adjudicated by two independent clinicians blinded to trial intervention with any discrepancies resolved by a third clinician as described previously [19].

### Secondary endpoints

The secondary endpoints include clinical, patient-centred, process and cost-effectiveness. These are detailed in Table 1.

**Table 1 Tab1:** Secondary endpoints

1. Clinical and patient-centred endpoints	• Myocardial infarction • Cardiac death • Cardiovascular death • Non-cardiovascular death • All-cause death • Unscheduled urgent coronary revascularisation • Hospital reattendance with suspected acute coronary syndrome • Proportion of patients with major bleeding (BARC 3–5) • Symptomatic status as assessed by the short form Seattle Angina Questionnaire (SAQ-7) up to 24 months of randomisation • Quality of life as assessed by the EQ-5D-5L up to 24 months of randomisation • Lifestyle changes including diet, smoking habit, and exercise at 24 months
2. Process endpoints	• Proportion of patients with allergy, anaphylaxis or acute kidney injury following study CTCA scan • Proportion of patients with clinically significant abnormal non-cardiac findings on study CTCA scan • Radiation dose from study CTCA scan • Proportion of patients undergoing non-study CTCA or invasive coronary angiography within 90 days of hospital attendance • Proportion of patients undergoing non-invasive stress test within 90 days of hospital attendance
3. Cost effectiveness endpoints	• Proportion of patients prescribed therapies for coronary artery disease • Proportion of patients undergoing non-invasive stress testing • Proportion of patients undergoing coronary revascularisation • Incremental cost per quality-adjusted life year (QALY) gained

*Abbreviations*: *BARC* Bleeding Academic Research Consortium definition of bleeding [20], *CTCA* computed tomography coronary angiogram

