### Study assessments

Study participants who are randomised to standard of care will not have any further study visits. Those randomised to CTCA with standard of care will be invited for an outpatient CTCA as soon as possible after their initial hospital attendance (ideally within 4 weeks of randomisation).

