### Management recommendations

Following CTCA reporting, results will be reviewed by members of the research team as soon as possible and a report forwarded to the participant, primary care physician and other healthcare professionals involved in clinical care as appropriate (Fig. 1). In patients with normal or near normal (< 10% stenosis) coronary arteries, no specific action will be required. However, for patients with mild (10–49%) or moderate (50–70%) non-obstructive coronary artery disease, the report will include recommendations to commence secondary preventative medical therapy (statin therapy alone or a combination of antiplatelet and statin therapy, respectively). For patients found to have untreated obstructive coronary artery disease (> 50% stenosis in the left main stem or > 70% stenosis in other coronary arteries), the report will include recommendations to provide lifestyle advice and commence antiplatelet and statin therapy, if there are no contra-indications, and they will also be offered a cardiology outpatient consultation (either face to face or telephone based) in accordance with local NHS policy, ideally within 2 weeks of the CTCA scan result.

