The role of CTCA in the assessment of patients with acute chest pain is less clear. Due to the large number of patients presenting to emergency departments worldwide every year, the use of further investigations to assess patients in whom the diagnosis of myocardial infarction is ruled out need to be both clinically efficacious and cost-effective. Economic modelling suggests that CTCA may be the most cost-effective modality for the diagnosis of important coronary artery disease in patients with suspected acute coronary syndrome in whom myocardial infarction is ruled out [3]. However, the likely effectiveness of this strategy at reducing myocardial infarction or cardiovascular death is highly dependent on the risk of cardiac events in the tested population. Two previous meta-analyses [32, 33] report data on ten trials of CTCA compared with functional testing in acute chest pain, mostly delivered in the North America. None of these trials were powered for subsequent myocardial infarction or death, and all were in very low risk populations with few events and a short duration of follow-up. Most participants received additional ancillary cardiac testing in the standard care arm. These analyses showed an increase in the diagnosis of coronary artery disease, invasive coronary angiography and coronary revascularisation in those receiving CTCA. A single trial of 600 patients, the CATCH (CArdiac cT in the treatment of acute CHest pain) trial, has reported longer term follow-up at a median of 18.7 months [34]. Major adverse cardiac events were observed in five patients in the CTCA group compared with fourteen patients in the standard of care group (hazard ratio 0.36 [95% CI 0.16 to 0.95]). Differences in myocardial infarction or cardiac death were not significant. Although event rates were low, this is the only trial of CTCA in acute chest pain that has shown a reduction in clinical outcomes in patients receiving CTCA.

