High-sensitivity cardiac troponin testing is already performed routinely in all patients with suspected acute coronary syndrome. As such, testing has major potential to improve the risk stratification of those patients in whom acute myocardial infarction is ruled out. Patients with intermediate cardiac troponin concentrations are at increased risk of cardiac events and are therefore more likely to benefit from further evaluation using CTCA and from secondary prevention in those found to have coronary artery disease. Currently, there is marked variation in the approach to the further evaluation and follow-up of patients after myocardial infarction has been ruled out, due to a lack of evidence from clinical trials to guide practice. Local pathways are based on expert opinion extrapolated from evidence derived in other patient populations. Consequently, current guidelines do not recommend any particular investigative approach for this large group of patients. As such, there is clinical equipoise to justify randomising patients to standard care or standard care with targeted CTCA in those with intermediate cardiac troponin concentrations.

The TARGET-CTCA trial will determine whether high-sensitivity cardiac troponin-guided CTCA can improve outcomes and reduce subsequent major adverse cardiac events in patients presenting to the emergency department who do not have myocardial infarction.

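### The process endpoint that pools non-study CTCA with invasive angiography combines two tests that may move in opposite directions between arms, so it may hide a rise in invasive angiography

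*Protocol article*

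**What the plan says.** Under Secondary endpoints, Table 1 gives this process endpoint: "Proportion of patients undergoing non-study CTCA or invasive coronary angiography", counted within 90 days of attendance. The study scan itself is not counted. The Statistical analysis section assigns binary secondary outcomes to logistic regression, so the line as written leads to one odds ratio for having either test.

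Other tests and procedures have their own lines: "Proportion of patients undergoing non-invasive stress test within 90 days of hospital attendance" among the process endpoints and "Proportion of patients undergoing coronary revascularisation" among the cost-effectiveness endpoints. Revascularisation does not stand in for angiography, because it leaves out purely diagnostic angiograms.

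Three other places bear on the direction of the two components:

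- On earlier acute chest pain trials, the Discussion says: "These analyses showed an increase in the diagnosis of coronary artery disease, invasive coronary angiography and coronary revascularisation in those receiving CTCA".
- Study assessments has the study scan done "ideally within 4 weeks of randomisation". Under Management recommendations, when the scan shows untreated obstructive disease, "they will also be offered a cardiology outpatient consultation", with a target of two weeks from the result.
- On usual practice, the Discussion reports "marked variation in the approach to the further evaluation and follow-up of patients after myocardial infarction has been ruled out", without giving a rate for any test.

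**The concern.** The two tests mean different things in the two arms. A non-study CTCA in a standard-care patient is contamination, because that patient has received the test under trial. An invasive angiogram in a CTCA-arm patient is often a downstream consequence of the intervention. Both score 1 on the same variable, so one can offset the other in the comparison between arms.

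Two questions would then be hard to read from the listed endpoint. The first is how much extra invasive testing the strategy generates, which bears on the secondary objective of safety and cost-effectiveness. The second is how much CTCA took place in the control arm, which is needed to interpret a primary result close to null. A small difference on the pooled line could be taken to mean little change in testing when invasive angiography had in fact risen.

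**Working it through.** **Inputs from the article.** Allocation is 1:1. The planned total is 2270, or 2270/2 = 1135 per arm; the extended total is 3170, or 3170/2 = 1585 per arm. The Sample size calculation gives 1081 per arm for 9% v 5.4% (a 40% relative reduction) at 90% power and two-sided 0.05. No 90-day rate is given for either test, so every rate below is an assumption.

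**The plan's own figure first.** With p̄ the mean of the two proportions,

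n = [1.96√(2p̄(1−p̄)) + 1.2816√(p₀(1−p₀) + p₁(1−p₁))]² / (p₀−p₁)²

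= [1.96√(2×0.072×0.928) + 1.2816√(0.0819 + 0.0511)]² / 0.036² ≈ 1081.4, that is 1082 per arm after rounding up. The stated figure is 1081. Then 2162 × 1.05 = 2270. The sample size reproduces and is not in dispute; it serves here only to fix the arm sizes.

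**When the pooled endpoint cancels.** Write c for non-study CTCA and i for invasive angiography, with 0 for standard care and 1 for the CTCA arm. If no patient has both tests,

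pooled difference = (i₁ − i₀) − (c₀ − c₁).

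The rise in angiography is reduced by the fall in non-study CTCA. That fall cannot exceed c₀, so control-arm use of non-study CTCA limits how much can be hidden.

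**Power.** At n per arm, with δ the absolute difference,

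power = Φ{[δ√n − 1.96√(2p̄(1−p̄))] / √(p₀(1−p₀) + p₁(1−p₁))}.

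Example, angiography alone at 4% v 8% and n = 1135: δ√n = 0.04 × 33.69 = 1.348; 1.96√(2×0.06×0.94) = 0.658; √(0.0384 + 0.0736) = 0.335. The argument is (1.348 − 0.658)/0.335 = 2.06, so power is 98%.

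**Results** (standard care v CTCA arm, no overlap; power at 1135 / 1585 per arm):

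| Non-study CTCA | Invasive angiography | Pooled endpoint | Power, pooled | Power, angiography alone |
|---|---|---|---|---|
| 6% v 2% | 4% v 8% | 10% v 10% | no difference to detect | 98% / 99.7% |
| 4% v 1% | 4% v 7% | 8% v 8% | no difference to detect | 88% / 96% |
| 3% v 0.5% | 4% v 8% | 7% v 8.5% | 27% / 35% | 98% / 99.7% |
| 10% v 2% | 5% v 10% | 15% v 12% (sign reversed) | 55% / 70% | over 99% |
| 2% v 0% | 5% v 10% | 7% v 10% | 73% / 86% | over 99% |
| 1% v 0.5% | 4% v 8% | 5% v 8.5% | 91% / 98% | 98% / 99.7% |

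**Effect of overlap.** If the two tests occur independently, the first row becomes 1 − 0.94×0.96 = 9.8% v 1 − 0.98×0.92 = 9.8%. The cancellation does not depend on the no-overlap assumption.

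**Direction of each component.** The rise in angiography rests on the Discussion's account of earlier trials and on the pathway: scan within about 4 weeks, then consultation within about 2 weeks of the result. That is about 6 weeks plus reporting time, so if randomisation is close to attendance, resulting angiograms can fall inside 90 days. The fall in non-study CTCA is inferred: the CTCA arm already has a scan that is not counted, while testing in standard care is unrestricted and varies.

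**The case against.** The strongest reply has four parts.

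- **The line is shorthand, and the analysis plan may split it.** The article does not call this endpoint a composite, as it does the primary, and tabulation by component is often left to the analysis plan, which is not shown. The split may indeed exist there. But Table 1 states one proportion for either test, and the analysis section sends such outcomes to one regression. The point concerns what is stated, not missing detail.
- **Opposite movement is not established.** This stands in part. A reader might infer that the two tests do move in opposite directions and that the endpoint will show no difference. The documents do not support that. The cited evidence on angiography comes from trials against functional testing in very low risk populations, and nothing states that non-study CTCA is common in standard care. The Background says most such patients go home without further investigation. If control-arm use is low, there is little to cancel.
- **Assumed rates can be chosen to cancel.** This is true of the first two rows of the table, which is why rows with partial or almost no masking stand beside them.
- **The information is not lost.** The Cost-effectiveness analysis section costs cardiac tests as items of resource use, so the two tests should be distinguishable in the data. That makes the split easy, but does not make the listed endpoint informative.

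The pairing also has a coherent meaning, any coronary anatomical imaging outside the study, and the exclusion criteria use the same pairing. That is a reason to allow the combined figure as a description.

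**Conclusion.** The point holds in a conditional form. As listed, the endpoint pools two tests that may move in opposite directions, and it may hide or reverse a rise in invasive angiography. A doubling of angiography from 4% to 8%, detectable alone with at least 98% power, gives a pooled difference of zero if non-study CTCA falls by 4 points, and 27–35% power if it falls by 2.5 points. If control-arm non-study CTCA is about 1%, the pooled line still detects the doubling with 91–98% power.

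These results rest on assumed rates, on a documented but unquantified rise in angiography, and on a fall in non-study CTCA inferred from the design. A reader should not conclude that masking will occur, that the combined figure must be dropped, or that the primary comparison is affected. This is one secondary process endpoint, and separating it is a cheap improvement.

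**What to change.** Replace the single line in Table 1, and the matching entry in the analysis plan, with two endpoints over the same window:

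1. the proportion undergoing invasive coronary angiography;
2. the proportion undergoing non-study CTCA, read as contamination in the standard-care arm and as repeat scanning in the CTCA arm.

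Analyse each by arm with the logistic regression already planned for binary outcomes. The combined proportion may stay as an optional descriptive extra without a formal comparison. If the analysis plan already separates the two, aligning the listed endpoint with it is enough. Settle the change before any analysis by arm.

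No new data are needed, because both tests must be identified to score the present endpoint. The cost is one more secondary comparison.

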### Exploratory endpoints

Lifestyle changes including diet, smoking habit and exercise will be captured using a questionnaire 24 months following enrolment. This will be used to determine whether the intervention compared to standard care results in changes to lifestyle or risk factors. To explore the pathophysiological mechanisms that influence cardiovascular risk, blood samples will be obtained and stored from consented participants, and we will perform visual and quantitative assessment of atherosclerotic plaque identified on CTCA imaging.

### Patient population

This trial will recruit at least 2270 participants from the emergency department or an equivalent acute medical admissions unit in secondary or tertiary care hospitals across the UK who will be randomised 1:1 to CTCA plus standard of care or standard of care alone. The inclusion criteria will be as follows: (i) presented to hospital with symptoms of suspected acute coronary syndrome; (ii) age ≥ 18 years old; and (iii) a maximum high-sensitivity cardiac troponin I or T concentration between 5 ng/L and the 99th centile. Exclusion criteria will be as follows: (i) diagnosis of myocardial infarction during index presentation; (ii) clear alternative diagnosis or participant requires further inpatient clinical assessment; (iii) CTCA or invasive coronary angiogram within 1 year from hospital attendance; (iv) inability to undergo CT scanning, for example due to severe renal failure (estimated glomerular filtration rate < 30 mL/min/1.73 m^2^) or major allergy to iodinated contrast media; (v) current pregnancy or breast feeding; (vi) inability to give informed consent; (vii) further investigation for coronary artery disease would not be in the patient’s interest, for example due to limited life expectancy, quality of life or functional status; or (viii) previous randomisation into the trial.

